## Methods/design

The study employs a Type 3 Hybrid design [76] to simultaneously examine the implementation process and effectiveness in five NICUs. To stagger implementation across the clinical sites, we use an incomplete stepped wedge design [77] (see Fig. 1). This design is more advantageous than conventional cluster randomized trials because it requires fewer NICUs (clusters), allows all NICUs to implement H-HOPE, and permits an estimate of treatment effects both within- and between-NICUs [77–80]. To eliminate systematic bias due to order of initiation, start dates were determined by a random number generator. Each NICU implements H-HOPE in 3 phases: Planning and Engaging (6 months), Executing (6 months), and Reflecting and Evaluating (2 months) [81, 82]. Implementation is followed by 6 months of Sustaining.

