#### Sample size and power for aim 2 effectiveness

Based on participating sites’ data, 542 infants will be eligible for the H-HOPE cohort during the 6-month Executing phase. Of the available infants, we expect to enroll at least 70% (*n* = 379 parent-infant pairs) and to retain 265 through 6-weeks following the infant’s discharge. During a 12-month period before H-HOPE implementation, 1084 eligible infants will be available for the Pre-H-HOPE Comparison Cohort in two sub-cohorts.

The first sub-cohort, the Consented Pre-H-HOPE Parent-Infant Units, is recruited at the same time as the Planning and Engaging phase at each site and will contribute to all outcome analyses (*n* = 542). The retention rates will be the same in the Consented Pre-H-HOPE sub-cohort and the H-HOPE cohort (*n* = 265). The second sub-cohort, the Non-Consented Pre-H-HOPE Infants (*n* = 542), will contribute only retrospective infant growth and cost data obtained from de-identified EHR and cost records in the 6 months prior to the start of Planning and Engaging. Based on our prior research, near medium to large effect sizes are expected for the primary outcomes of infant growth and health care utilization following discharge [49, 57] and the secondary hospital cost outcome [58]. Using the STATA package *stepped wedge* [84], the power analysis found that there will be at least 80% of power to detect a medium effect of Cohen’s *d* = − 0.50 at a significance level of α = .05 in this stepped wedge design with 4 sites and an average of at least 50 subjects per site (or 200 in total) across 4 staggered time points, assuming the intra-class correlation coefficient (ICC) is .1, a common ICC found in health and behavioral research [85, 86]. Assuming ICC as .05, which is common ICC health cost analysis [87–89], research would require at least 30 subjects per site (or 120 in total). Thus, in this proposed study, the anticipated total sample size of 265 will be adequate to detect a medium effect for all outcome measures.

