The Aim 3 sample includes hospital personnel and parents receiving H-HOPE at each site. Consented H-HOPE parents will be randomly selected (15 parents per site, 75 total) to be interviewed prior to discharge and when their infant is 6-weeks post discharge. Purposively selected hospital personnel include at least one hospital administrator, NICU leadership (e.g. medical director and nurse manager), clinical site H-HOPE team members (2–4 per site), and selected staff who work in the NICU (10 per site) who have delivered H-HOPE, especially champions and non-supporters. Each of these selected hospital personnel will participate in 3 short qualitative interviews about their experience with H-HOPE. In addition, all registered staff nurses who work at least 50% in the NICU will complete a brief survey regarding engagement and burnout during the three project phases.

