### Implementation study conditions

Infants and parents in the Pre-H-HOPE Comparison Cohort receive usual NICU care and parent interactions with NICU staff.

The H-HOPE Cohort of infants and parents receive H-HOPE in-hospital and during the transition to home. Four parent-directed participatory guidance sessions offer social support to parents and help them learn the nuances of preterm infant behavior and how to interact with their infant and provide Massage+. The initial in-hospital session occurs when H-HOPE begins. Preparing for the transition to home begins during the second in-hospital session shortly before discharge, and continues with sessions at 2–3 days and 7–15 days post-discharge via screen time. The infant-directed multi-sensory component of H-HOPE Massage+, is administered for 15 min prior to a feeding twice daily, starting when the infant is physiologically stable and ready for social interaction (≈ 31–32 weeks PMA for infants < 30 GA at birth). Twice daily administration was selected based on our previous research [11, 12, 14, 43, 50, 52–54, 56, 90–92]. Ideally, parents would always administer Massage+, however few parents are able to visit twice daily. Therefore, trained staff will provide the intervention in the parents’ absence. Parents will continue the Massage+ at home twice daily until 1-month CA. In our previous research with low income minority parents, 95% continued Massage+ at home [43, 52].

To assess H-HOPE fidelity during Executing at each site, we document completeness and quality of services provided for each parent-infant unit, as recommended in recent studies [93, 94]. Completeness of services in-hospital and during the transition to home is recorded in the EHR and assessed as part of Aim 1. The quality of H-HOPE services is examined periodically using standardized forms by site staff to ensure that fidelity at that site is maintained over time.

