#### Aim 3 secondary implementation outcome measures

Aim 3 uses mixed methods analyses to integrate data collected for this aim regarding influences (facilitators or barriers) in each of the 5 CFIR domains with data from Aim 1 (implementation success) and Aim 2 (effectiveness for the primary infant outcomes). Data specific for Aim 3 include: qualitative interviews with hospital personnel and parents, H-HOPE team meeting records, research team observation notes, nurse survey data, and fidelity data from H-HOPE records. Separate interview guides for hospital personnel and parents include questions about domains and constructs within the CFIR framework relevant to their experience with H-HOPE. Hospital personnel are interviewed at 3 time points (Planning and Engaging, end of Executing, and end of Sustaining). Data about individual characteristics that influence implementation come from registered staff nurse surveys conducted at the same time as the interviews. Parents are interviewed twice: close to discharge and again after discharge when the infant has been home for 6 weeks.

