### Study procedures

#### Overall study coordination

Procedures for this multisite complex implementation and evaluation study, are coordinated within three Centers: the Implementation Center, the Quantitative Data Center, and the Qualitative and Mixed Methods Data Center. Each Center is guided by a co-investigator who works collaboratively to facilitate overall project coordination and management.

The Implementation Center coordinates the implementation of H-HOPE at each clinical site, working closely with the H-HOPE Clinical Site Implementation Team. Each site’s H-HOPE team is comprised of the Clinical Site Nurse, NICU leadership and other clinicians. Collaboratively with the co-investigator and the study’s Project Director, the site H-HOPE team develops the site-specific NICU protocol and plan for staff training, coordinates the implementation process in the NICU, and serves as champions who provide resources and support for staff throughout implementation.

During the Planning and Engaging phase, the Implementation Center will train the clinical site’s H-HOPE Implementation team. The H-HOPE Team in collaboration with the Center Director, will identify the necessary processes for establishing the H-HOPE program as standard of care, taking into account the NICU culture and their capability for adaptation. During the Executing phase, the NICU will implement H-HOPE according to their plan. During the Reflecting and Evaluating phase, the H-HOPE Implementation team will participate in preparing a report describing the effectiveness of the H-HOPE program on the infants and parents in their NICU, as well as hospital personnel. This report will be shared with hospital administrators and NICU leadership to provide evidence for sustaining or ending the H-HOPE program. During independent Sustaining, the H-HOPE Implementation Team can contact the Implementation Center at any time for additional consultation.

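### The 10 NICU staff interviewees per site must already have delivered H-HOPE, yet their first of three interviews falls in Planning and Engaging, before delivery begins

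*Protocol article*

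**What the plan says.** The Aim 3 sample is described in the last paragraph of the protocol article's section on sample size and power for Aim 2. Hospital personnel are chosen purposively. One group carries no delivery condition: "at least one hospital administrator, NICU leadership (e.g. medical director and nurse manager), clinical site H-HOPE team members (2–4 per site". The other group does: "selected staff who work in the NICU (10 per site) who have delivered H-HOPE, especially champions and non-supporters". The next sentence applies to everyone chosen: "Each of these selected hospital personnel will participate in 3 short qualitative interviews about their experience with H-HOPE".

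The section on Aim 3 secondary implementation outcome measures fixes the timing: "Hospital personnel are interviewed at 3 time points (Planning and Engaging, end of Executing, and end of Sustaining". It adds that the registered nurse surveys run alongside these interviews.

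Methods/design gives the order and length of the phases as "Planning and Engaging (6 months), Executing (6 months), and Reflecting and Evaluating (2 months", followed by six months of Sustaining. Overall study coordination says when H-HOPE starts: "During the Executing phase, the NICU will implement H-HOPE according to their plan". The consented comparison sub-cohort "is recruited at the same time as the Planning and Engaging phase at each site", and under Implementation study conditions, "Infants and parents in the Pre-H-HOPE Comparison Cohort receive usual NICU care and parent interactions with NICU staff".

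**The concern.** A person can be selected for having delivered H-HOPE only after delivery has begun, but the first interview comes before that. A site that follows the selection rule has no bedside staff to interview in the first round. A site that follows the interview schedule must set the selection rule aside. The article does not say which gives way, and five NICUs with staggered starts could settle it differently.

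The same condition shapes who can be heard later. A nurse who avoids or declines H-HOPE throughout never qualifies, although the sentence that sets the condition asks for non-supporters in particular.

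Aim 3 looks for facilitators and barriers associated with implementation success, which includes Reach and Degree of Implementation, and the Aim 3 analyses call for a narrative and matrix for each site over time. If front-line staff have no first-round interview, and staff who never deliver have none at all, the interviews are thinnest where barriers to uptake would be expected. A missed pre-implementation interview cannot be recovered once Executing has begun.

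**Working it through.** The article states no sample-size or power figure for this point, so there is none to reproduce. The check is a comparison of the stated rules, followed by a count.

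**1. Can both rules be met?**

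- Selection: the 10 staff per site have, in the past tense, delivered H-HOPE (Aim 3 sample paragraph).
- Number of interviews: three for each selected person (same paragraph).
- Timing: the first of the three is in Planning and Engaging (Aim 3 measures).
- Start of delivery: Executing, which follows the six months of Planning and Engaging (Methods/design; Overall study coordination).
- Cross-check: the consented comparison cohort is recruited during Planning and Engaging and receives usual care. The Fig. 1 legend also places comparison data collection in that period. Delivering H-HOPE then would contaminate the Aim 2 comparison, so early delivery is not a plausible way out.

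At the first time point nobody meets the selection rule. Staff selected once delivery is under way can give at most two of the three interviews. The article describes no separate first-round sample of bedside staff and no rule for replacing interviewees.

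**2. How many interviews are affected?**

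- Staff under the delivery condition: 10 × 5 = 50. All five NICUs count, because Study setting and sample treats Sites 2 and 3 separately for Aims 1 and 3.
- Other personnel per site: at least 1 administrator, leadership (two examples given, no number) and 2 to 4 team members. Assume 1 administrator and 2 leaders.
- Roster per site: 1 + 2 + 2 + 10 = 15, up to 1 + 2 + 4 + 10 = 17.
- Roster over five sites: 5 × 15 = 75 to 5 × 17 = 85.
- Share of first-round interviews without an eligible interviewee: 50/85 = 59% to 50/75 = 67%.
- Share of all three rounds: 50/(3 × 85) = 50/255 = 20% to 50/(3 × 75) = 50/225 = 22%.

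Sensitivity to the assumed roster: the affected staff remain a majority of the first round as long as other personnel number 9 or fewer per site (10/19 = 53%). At 10 others the share is exactly half.

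**3. Who is left out throughout?**

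Staff who never deliver H-HOPE fail the condition at every time point. Reluctant staff who nonetheless deliver it do qualify. The documents do not say how many staff would never deliver, so this loss cannot be sized.

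**The case against.** The strongest reply is that this is loose wording in a condensed article. Asking for three interviews makes sense only if the authors meant staff who deliver H-HOPE at some point in the study, and the first interview is then feasible. Details such as the date of selection are commonly left to the full protocol. That reading is possible. But the criterion and the timing are both stated here and they conflict, so this is not a detail merely left out. The milder reading also still excludes staff who never deliver.

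A reader might infer that front-line staff have no baseline at all, or that change over time cannot be read. The documents do not support that. All registered nurses working at least half-time in the NICU are surveyed at the same times as the interviews, whether or not they deliver H-HOPE. Administrators, leaders and team members can be interviewed in Planning and Engaging. Meeting records and observation notes also feed Aim 3, and the matrices are built per site, not per nurse. What remains is that the survey covers engagement and burnout only, so it does not replace interviews organised around the CFIR domains.

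A reader might also infer that the plan selects on its outcome. The success measures are site-level, and H-HOPE is introduced as standard of care with trained staff giving Massage+ when parents are absent, so some non-supporters will have delivered it. The exclusion is partial.

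Finally, one might extend the point to the parents, who are drawn only from those receiving H-HOPE. Interviewing recipients about their experience is a legitimate choice. The draw is random, and the Aim 2 covariates show that partial exposure is expected. That is not an error.

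**Conclusion.** The point holds as a contradiction between two stated rules. Read as written, none of the 50 NICU staff is eligible for the first interview, and staff who never deliver H-HOPE are excluded from the interviews by criterion. The 50 follows directly from the article. The 59–67% rests on one administrator and two leaders per site and on the literal wording; it is a share of the planned roster, not a demonstrated loss of interviews.

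The reach is limited. Only the qualitative part of Aim 3 is affected, and partial baseline information remains. The Aim 1 success measures, the Aim 2 estimates and the Aim 2 power calculation are untouched. It is worth correcting because the change is small and has to be made before the first site's Planning and Engaging interviews to be of full use.

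**What to change.** Reconcile the Aim 3 sample paragraph with the Aim 3 measures section:

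- Replace the past-delivery condition for the 10 staff per site with staff expected to care for H-HOPE-eligible infants.
- Select them during Planning and Engaging, including likely champions and likely non-supporters.
- Keep them for all three interviews whether or not they later deliver H-HOPE.

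The cost is a change of wording and an earlier sampling list, with the same number of interviews. Study status reports that no site had begun implementation and nobody had been enrolled at submission. The downside is small: some of those selected may leave or never deliver H-HOPE, and their replacements will lack a first interview.

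Two additions that may suggest themselves are better avoided. Reserving places for low deliverers found in the EHR during Executing would bring in people without a first interview, and the article describes the Aim 1 EHR data as de-identified and aggregated, with no staff-level listing. Stratifying the parent draw by services received would not work cleanly, because the first parent interview precedes discharge and two of the four guidance sessions come after it.

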### Implementation study conditions

Infants and parents in the Pre-H-HOPE Comparison Cohort receive usual NICU care and parent interactions with NICU staff.

The H-HOPE Cohort of infants and parents receive H-HOPE in-hospital and during the transition to home. Four parent-directed participatory guidance sessions offer social support to parents and help them learn the nuances of preterm infant behavior and how to interact with their infant and provide Massage+. The initial in-hospital session occurs when H-HOPE begins. Preparing for the transition to home begins during the second in-hospital session shortly before discharge, and continues with sessions at 2–3 days and 7–15 days post-discharge via screen time. The infant-directed multi-sensory component of H-HOPE Massage+, is administered for 15 min prior to a feeding twice daily, starting when the infant is physiologically stable and ready for social interaction (≈ 31–32 weeks PMA for infants < 30 GA at birth). Twice daily administration was selected based on our previous research [11, 12, 14, 43, 50, 52–54, 56, 90–92]. Ideally, parents would always administer Massage+, however few parents are able to visit twice daily. Therefore, trained staff will provide the intervention in the parents’ absence. Parents will continue the Massage+ at home twice daily until 1-month CA. In our previous research with low income minority parents, 95% continued Massage+ at home [43, 52].

To assess H-HOPE fidelity during Executing at each site, we document completeness and quality of services provided for each parent-infant unit, as recommended in recent studies [93, 94]. Completeness of services in-hospital and during the transition to home is recorded in the EHR and assessed as part of Aim 1. The quality of H-HOPE services is examined periodically using standardized forms by site staff to ensure that fidelity at that site is maintained over time.

The H-HOPE Implementation Support Package consists of 2 components. A multimedia web-based program provides materials and training which are available to parents and staff on the Pathways.org website (www.Pathways.org). Interactive assistance from the investigative team to each site provides NICU-specific consultation throughout the 3 phases of implementing H-HOPE. This consultation has been shown to facilitate implementation [82, 95]. On line webinars will be supplemented by in person training and support at the infant’s bedside, especially when the staff administer H-HOPE for the first time. Each site will have several master trainers. A program for master trainers will be developed using examples from the first two sites trainings.

### Measures

#### Aim 1 primary implementation outcome measures

We examine three measures of success recommended for late-phase implementation by Proctor et al. [72]. Sustainability measures whether the site is providing H-HOPE. Reach measures the proportion of eligible parent-infant units who receive H-HOPE at that site. Degree of Implementation measures the mean H-HOPE services received per parent-infant unit. The research team will consult with each site to build within the EHR infant eligibility for H-HOPE, documentation of Massage+ and the parent participatory guidance sessions. These success measures will be obtained from each site’s EHR which will record eligibility and receipt of H-HOPE parent and infant services. If the site chooses to discontinue H-HOPE, we will conduct the final interview and end evaluation.

#### Aim 3 secondary implementation outcome measures

Aim 3 uses mixed methods analyses to integrate data collected for this aim regarding influences (facilitators or barriers) in each of the 5 CFIR domains with data from Aim 1 (implementation success) and Aim 2 (effectiveness for the primary infant outcomes). Data specific for Aim 3 include: qualitative interviews with hospital personnel and parents, H-HOPE team meeting records, research team observation notes, nurse survey data, and fidelity data from H-HOPE records. Separate interview guides for hospital personnel and parents include questions about domains and constructs within the CFIR framework relevant to their experience with H-HOPE. Hospital personnel are interviewed at 3 time points (Planning and Engaging, end of Executing, and end of Sustaining). Data about individual characteristics that influence implementation come from registered staff nurse surveys conducted at the same time as the interviews. Parents are interviewed twice: close to discharge and again after discharge when the infant has been home for 6 weeks.

### Study procedures

#### Overall study coordination

Procedures for this multisite complex implementation and evaluation study, are coordinated within three Centers: the Implementation Center, the Quantitative Data Center, and the Qualitative and Mixed Methods Data Center. Each Center is guided by a co-investigator who works collaboratively to facilitate overall project coordination and management.

The Implementation Center coordinates the implementation of H-HOPE at each clinical site, working closely with the H-HOPE Clinical Site Implementation Team. Each site’s H-HOPE team is comprised of the Clinical Site Nurse, NICU leadership and other clinicians. Collaboratively with the co-investigator and the study’s Project Director, the site H-HOPE team develops the site-specific NICU protocol and plan for staff training, coordinates the implementation process in the NICU, and serves as champions who provide resources and support for staff throughout implementation.

During the Planning and Engaging phase, the Implementation Center will train the clinical site’s H-HOPE Implementation team. The H-HOPE Team in collaboration with the Center Director, will identify the necessary processes for establishing the H-HOPE program as standard of care, taking into account the NICU culture and their capability for adaptation. During the Executing phase, the NICU will implement H-HOPE according to their plan. During the Reflecting and Evaluating phase, the H-HOPE Implementation team will participate in preparing a report describing the effectiveness of the H-HOPE program on the infants and parents in their NICU, as well as hospital personnel. This report will be shared with hospital administrators and NICU leadership to provide evidence for sustaining or ending the H-HOPE program. During independent Sustaining, the H-HOPE Implementation Team can contact the Implementation Center at any time for additional consultation.

The Quantitative Data Center provides oversight and coordination for all quantitative data-related operations and conducts the quantitative data analyses for Aim 1 (degree of implementation) and Aim 2 (effectiveness). Prior to Planning and Engaging, the Center works with each site’s informatics team to modify their EHR build so the H-HOPE eligibility, initiation and specific services received can be documented directly in the EHR. The Center also oversees the REDCap database construction and management for participant screening, study enrollment, eConsenting, study monitoring, and quantitative data collection. During implementation at each site, the Center works closely with each site to obtain relevant data throughout the study, shares site results and helps prepare the report that the site administrative team will use to decide whether to continue H-HOPE as the standard of care. Each site has a H-HOPE research team that is responsible for consenting both pre-H-HOPE and H-HOPE parents, facilitating and monitoring data collection, and coordinating data collection and transfer with the data Centers.

The Qualitative and Mixed Methods Data Center manages and analyzes all qualitative and mixed methods data-related operations. The primary focus of the Center is ongoing mixed methods data analysis and interpretation to address Aim 3. The qualitative interview data are managed within the Center and analyzed as described below. The relevant quantitative data are obtained from the Quantitative Data Center. At each site, the Center works with the H-HOPE team to obtain H-HOPE team meeting records and to complete interviews with selected hospital personnel and selected H-Hope parents.

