**Discussion:**

This study builds on the CFIR, adding Sustaining H-HOPE to observe what happens when sites begin to maintain implementation without outside support, and extends its use to the NICU acute care setting. Our mixed methods analysis systematically identifies key facilitators and barriers of implementation success and effectiveness across the five domains of the CFIR. Long term benefits have not yet been studied but may include substantial health and developmental outcomes for infants, more optimal parent-child relationships, reduced stress and costs for families, and substantial indirect societal benefits including reduced health care and special education costs.

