### Preparing NICUs to adapt H-HOPE as the standard of care

To reduce the gap between research and implementation, clinicians need a strategy to introduce an early behavioral intervention involving parents within the high-acuity NICU. Our implementation strategy integrates our experience conducting H-HOPE and a well-established implementation model, the Consolidated Framework for Implementation Research (CFIR) [59]. The CFIR identifies influences (facilitators and barriers) that affect successful implementation within five domains: intervention characteristics, outer setting (the hospital and external events and stakeholders), inner setting (NICU), implementers’ individual characteristics, and the implementation process. We selected the CFIR because the framework integrates the best features of previous models [59] and captures the complexity of real-world implementation to identify site-specific factors and patterns across cases [60, 61]. The framework has been used for diverse interventions in inpatient, clinic and community settings. A systematic review in 2016 identified 26 empirical studies using the CFIR, [62] and there are numerous studies published since then [43, 63–71]. However, only two previous studies occurred in a high acuity inpatient setting (adult acute care units) [63, 70] and no prior studies include the NICU setting. The CFIR provides a systematic approach that will be used to guide the process of implementing H-HOPE in NICUs, to recognize facilitators of successful implementation, and to identify and address implementation barriers across different sites. NICUs will use the CFIR process, which includes three phases: Planning and Engaging, Executing, and Reflecting and Evaluating. We modified the CFIR implementation process by adding a final phase of sustaining H-HOPE without continued support from the research team, because sustaining is a critical goal of implementation [72, 73].

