### Study aims

#### Aim 1 (implementation success)

Identify the degree of implementation success at each clinical site every 2 months from Executing through 6 months after supported implementation ends (*primary implementation outcome)*. Success measures include: Sustainability (offering H-HOPE), Reach (% of eligible parent-infant units receiving H-HOPE) and Degree of Implementation (mean H-HOPE services received).

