## Discussion

This study builds on one of the most widely used and systematic implementation frameworks, the CFIR, and extends its use to the NICU acute care setting. We adapted the 3-phase CFIR implementation model by adding Sustaining to explicitly observe what happens when sites begin to maintain implementation without outside support. Our mixed methods analysis systematically identifies key facilitators and barriers of implementation success and effectiveness across the five domains of the CFIR. The five participating NICUs were purposively selected to represent different acuity levels, number of beds, locations and populations served. This comprehensive approach allows us to examine both the final level of implementation success and different patterns by site over time.

Results of our analysis will identify common and site-specific implementation facilitators and barriers as well as ways sites overcame barriers. Findings will be widely disseminated to guide future expansion of H-HOPE as the standard of care. Study results will make major contributions to implementation science, especially for the introduction of complex evidence-based programs into the challenging high-acuity environment of the NICU. If the five sites in this study are successful in sustaining the program, H-HOPE will be ready for widespread adoption nationwide.

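### Sustaining is described as free of outside support, yet research-team consultation stays available on request and the Aim 1 measures take no account of its use

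*Protocol article*

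**What the plan says.** Three places in the protocol article define Sustaining by the absence of support. The Abstract (Discussion paragraph) gives its purpose as "adding Sustaining H-HOPE to observe what happens when sites begin to maintain implementation without outside support". The Background section on preparing NICUs describes "adding a final phase of sustaining H-HOPE without continued support from the research team". The main Discussion repeats the purpose: "adding Sustaining to explicitly observe what happens when sites begin to maintain implementation without outside support". Consistently with these, Aim 1 measures implementation success "every 2 months from Executing through 6 months after supported implementation ends".

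The section Implementation study conditions says what the support is. The support package has two components, a web-based programme and help from the research team. The second is described as follows: "Interactive assistance from the investigative team to each site provides NICU-specific consultation throughout the 3 phases of implementing H-HOPE". The three phases are Planning and Engaging, Executing, and Reflecting and Evaluating. Sustaining comes after them.

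Overall study coordination then says of the last phase: "During independent Sustaining, the H-HOPE Implementation Team can contact the Implementation Center at any time for additional consultation".

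Under Measures, Aim 1 has three measures: whether the site is providing H-HOPE (Sustainability), the share of eligible parent-infant units reached (Reach), and the average amount of service delivered (Degree of Implementation). The Aim 1 analysis is descriptive.

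**The concern.** The phase was added so that readers could see what sites do once help is withdrawn. If the same team that provided the help can still be called on, a site that kept the programme going with that help gets the same Aim 1 score as a site that managed alone. The two cases mean different things for a NICU that would adopt H-HOPE without a research centre to call.

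At stake is the interpretation of the primary implementation outcome in its post-support window. Aim 3 inherits the problem, because it links facilitators and barriers to the levels of success found in Aim 1. The Discussion also rests its view of readiness for national adoption on the five sites succeeding in sustaining the programme.

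**Working it through.** This is a check of consistency. The article gives no figure for this point, so there is none to reproduce.

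**Step 1: what is claimed.** The Abstract and the Discussion both claim observation of sites with no outside support. The Background claims no continued support from the research team. The claim in the Abstract and Discussion is absolute. The claim in the Background could be read as ruling out ongoing support only.

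**Step 2: what is provided.** Consultation from the Implementation Center may be requested in Sustaining at any time, with no stated limit. The Center belongs to the research organisation, so its help is outside support in the sense of the Abstract and Discussion.

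**Step 3: whether this is the same kind of help.** Implementation study conditions counts consultation by the investigative team as a component of the support package and assigns it to the three earlier phases. The article adds there that such consultation has been shown to help implementation. Calling the Sustaining-phase help additional suggests more of that kind. The mode differs, though. In the earlier phases consultation is regular and accompanied by bedside training, while in Sustaining the site must ask for it.

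**Step 4: whether the outcome separates the two cases.** None of the three Aim 1 measures has an element for help received. A site providing H-HOPE is scored as sustaining whether or not it called.

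**Step 5: how much of the outcome could be touched.** Phase lengths come from Methods/design, and the two-month interval comes from Aim 1.

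- Executing 6 + Reflecting and Evaluating 2 + Sustaining 6 = 14 months per site
- 14 / 2 = 7 two-monthly assessments, of which 6 / 2 = 3 fall in Sustaining

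This 3 of 7 is the maximum exposure. It does not estimate how many assessments a consultation would change, and the article gives no expected rate of contact from which to estimate that.

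**Step 6: Aim 2.** The H-HOPE cohort for effectiveness is drawn from the six-month Executing phase (Sample size and power), before Sustaining begins. The effectiveness comparison and its power are not affected.

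**The case against.** The strongest reply is that on-request contact is not continued support. Regular consultation led by the research team stops, and leaving a line open fits both the Background wording and the Aim 1 phrase about supported implementation ending. This stands for those two places. It does not rescue the Abstract and the Discussion, which exclude outside support without qualification.

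Second, a reader might infer that Sustaining cannot show unsupported sustainability at all. The documents do not support that. A site that never calls is in effect unsupported. The difficulty is that the Aim 1 results would not show which sites those are.

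Third, a reader might infer that consultation goes wholly unrecorded. That is not established either. Aim 3 draws on team meeting records, research-team observation notes and personnel interviews at the end of Sustaining, and these may capture some contacts. A contact log is also the sort of operational detail an article may leave to the full protocol, so its absence here is not itself a fault. But no such source is said to feed the Aim 1 measures, and a log kept elsewhere would not remove the contradiction in the wording.

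Fourth, it is tempting to say that struggling sites call most, so that results are biased towards success and barriers are hidden. Nothing in the documents supports a direction. A call could equally expose a barrier through the records and interviews just mentioned. Nor does the article define a pooled proportion of sites sustained, so the observation that one site in five is 20 percentage points is arithmetic about five sites and does not measure bias.

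Finally, the Discussion sentence on national adoption speaks of success in sustaining the programme and does not say that sites did so independently.

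**Conclusion.** The point holds in a limited form. The Abstract, Background and Discussion describe Sustaining as free of outside or continued research-team support. Overall study coordination leaves a component of the support package available on request throughout that phase, and the Aim 1 measures do not take its use into account. As described, the results support a statement about sustainability with consultation available on request. They do not support one about sustainability without support.

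The size and direction of any effect are unknown. The possible reach is bounded by the 3 Sustaining assessments per site, and the actual effect could be nil if no site calls. The conclusion assumes that consultation in Sustaining is of the same kind as in the earlier phases, though site-initiated and probably less intensive. It is a matter of what may be concluded from the primary implementation outcome. It does not undermine the design, and Aim 2 is untouched.

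**What to change.** Keep the access. Then:

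1. Have the Implementation Center log each Sustaining-phase contact prospectively: date, site, who initiated it, topic and time spent.
2. Report the amount of consultation by site and two-month period beside Sustainability, Reach and Degree of Implementation. Amount is preferable to a yes/no classification, which would treat a brief query like substantive help.
3. Enter the amount in each site's Aim 3 matrix, so that reliance on the Center can be weighed among the influences on success.
4. In the Abstract, Background and Discussion, restate the claim as sustaining without scheduled support, with consultation on request. Keep the stronger description only for sites with no substantive logged consultation. Define substantive before the first site enters Sustaining.

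The cost is a small logging burden at an existing centre and an extra row in descriptive tables. Fewer sites may count as independently sustained. The log has to start prospectively to be complete. The Study status section says implementation had not begun at any site when the article was submitted, so on that timeline it could cover every site.
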